### Secondary aims

To explore changes in plasma sulfate concentrations over time, by correlating with the fractional excretion index (FEI) of sulfate at 1, 3, 7, 14 and 28 days of age, for VP/EP infants exposed to antenatal MgSO_4_ versus unexposed.To explore whether, for VP/EP infants exposed to antenatal MgSO_4_, known loss-of-function variants in the maternal/infant *SLC13A1* or maternal *SLC13A4* genes are associated with lower plasma sulfate concentrations at 7 and 28 days of age.To explore the impact of antenatal, neonatal and genetic factors (including MgSO_4_ dose, FEI sulfate and sulfate transporter gene variants) on neonatal sulfate concentrations within the first 28 days after birth, and to establish a population pharmacokinetic model for sulfate in the VP/EP infant.To explore potential relationships between plasma sulfate concentration in VP/EP infants at 7 days of age and IVH (worst grade during neonatal intensive care unit (NICU) admission), ROP (worst stage in early infancy) or capillary haemangiomas (number and size in infancy).

## Methods

Prospective observational study at three tertiary NICUs in South-East Queensland, Australia: Mater Mothers’ Hospital (MMH)—lead study site, Royal Brisbane and Women’s Hospital (RBWH) and the Gold Coast University Hospital (GCUH).

### Participant cohort

#### Inclusion criteria

Preterm infants born at 24^+0^ to 31^+6^ weeks of gestation and admitted to NICU (figure 1).

**Figure 1 F1:**
[figure not shown]
Protocol with details of biological sample collection. NICU, neonatal intensive care unit.

#### Exclusion criteria

Major congenital/chromosomal abnormality likely to adversely affect survival or neurodevelopmental outcome. Maternal age less than 16 years.

### Recruitment

Women and their partners (‘parents’) are approached before or after delivery to explain the study, and consent is sought within the first few days after delivery.

Recruitment commenced at MMH in July 2015 and at RBWH in August 2015. To accelerate recruitment, the study was expanded to GCUH in June 2019.

Parents of surviving infants recruited into a pilot study of postnatal sulfate concentrations conducted at the lead study site in 2013–2014 (N=52) were contacted for consent to follow-up and inclusion in this study.

### Biological sample collection

#### Blood sample collection for *all* participants to address the primary aims

A blood sample (0.5 mL) is collected on day 7 of age (±1 day) for plasma sulfate and magnesium measurement (figure 1).

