### Sulfate deficiency in the neonatal period following very preterm birth

Infants born <32 weeks gestation (very preterm (VP)/extremely preterm (EP)) will likely rapidly become deficient in sulfate due to three factors: (1) minimal dietary supply of free inorganic sulfate in breast milk (including colostrum),^32^ total parenteral nutrition solutions, and human milk fortifiers; (2) negligible capacity to generate sulfate from sulfur-containing amino acids due to low expression of cysteine dioxygenase gene^14 33^; (3) immature renal function including low expression of SLC13A1, with limited ability to reabsorb filtered sulfate.^15 21 34 35^

Maturation of various physiological systems in the preterm infant accelerates postnatally, for example, surfactant protein production^36^ and renal maturation.^35^ Hence, it is likely that preterm infants rapidly switch on expression of the cysteine dioxygenase and SLC13A1 genes after birth, and thus develop the capacity to generate and retain sulfate within days to weeks.

A pilot study at the lead study site (online supplemental file 1) demonstrated that, as predicted, sulfate concentrations among VP/EP newborns fell rapidly over the first week after birth, before stabilising and increasing thereafter. As VP/EP infants are born during a critical period of brain development, they are likely to be highly vulnerable to adverse effects of hyposulfataemia. This window of vulnerability also coincides with the occurrence of IVH and ischaemia (later manifesting as periventricular leukomalacia (PVL)), both predisposing factors for adverse neurodevelopmental outcome. The pilot study at the lead study site (online supplemental file 1) also showed that antenatal MgSO_4_ largely mitigates the occurrence of very low concentrations in the preterm infant; boosting sulfate to supra-physiological concentrations at birth which then decay to normal or adequate concentrations by which time the infant’s capacity to generate and retain sulfate may have matured. However, common reduced-function variants of renal *SLC13A1* and placental *SLC13A4* sulfate transporter genes may impede the efficacy of antenatal MgSO_4_ treatment to boost fetal sulfate concentrations.

10.1136/bmjopen-2023-076130.supp1Supplementary data

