### Antenatal and neonatal data

Details regarding dose/duration/timing of the loading dose and maintenance infusion of MgSO_4_, along with maternal weight, are recorded.

Antenatal/maternal and delivery data are also recorded, including antenatal steroid administration, primary reason for preterm birth, whether inborn or outborn from tertiary centre, mode of birth, and date and time of birth.

Neonatal data collected includes expected date of delivery, gestational age and weight at birth, sex, singleton/multiple, Apgar scores (1 and 5 min). CRIB score^49^ data are collected if available. Details of potential factors affecting plasma sulfate concentration are also noted, specifically date/time of any blood transfusions administered within the blood sampling period, and date when ferrous sulfate commenced.

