### Sample size considerations for secondary aims

#### Secondary aim 1

Using data obtained in a pilot study undertaken at the lead study site (online supplemental file 1), 231 infants exposed to antenatal MgSO_4_ are required to produce a two-sided 95% CI (SD 154, CI width 40). Additionally, 160 infants *not* exposed to antenatal MgSO_4_ are required to produce a two-sided 95% CI (SD 32, width 10).

#### Secondary aim 2

The sample size is based on the combined allelic frequencies of the *SLC13A1* (0.26% p.Arg12Ter and 29.5% p.Asn174Ser) and *SLC13A4* (0.05% p.Ser139Valfs, 0.02% p.Leu72Serfs and 0.05% p.Phe309Cys) gene variants from the NCBI database, and data from a pilot study undertaken at the lead study site showing low neonatal blood sulfate concentrations at 7 days in 10/21 (48%) and at 28 days in 5/15 (33%) of infants whose mothers received MgSO_4_ (online supplemental file 1). Since this aim encompasses two time points, the type I error will be set at 0.025 rather than 0.05 (using Bonferroni’s correction). Additionally, assuming power of 90%, 30% of infants will have a gene variant and in this group 90% will have low sulfate, compared with 30% in the non-variant group, 60 infants and their mothers will need to be included in the study at 7 days of age. At 28 days of age, with the same parameters, however, if fewer infants with a gene variant (80%) have low sulfate and more infants without a gene variant (20%) have low sulfate, 35 infants are required. These infants will be a subset of secondary aim 3.

#### Secondary aim 3

Using data obtained in a pilot study undertaken at the lead study site (online supplemental file 1), 121 infants exposed to antenatal MgSO_4_ are required to develop a multivariate model to assess the relationship between low plasma sulfate concentration with the dose of MgSO_4_ administered, FEI sulfate in the first week after birth, sampling time-point and absence or presence of known loss of function mutations, using the assumption that ten infants with low sulfate are required for potential independent variables.

Blood and urine samples from 300 infants (with or without antenatal MgSO_4_ exposure) taken within 24 hours after delivery, and at 3, 7, 14, 28 days of age will provide sufficient data to create and fit a population pharmacokinetic model for sulfate in the preterm infant using non-linear mixed-effects modelling.^55 56^

#### Secondary aim 4

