### Statistical methods

#### Primary aims 1 and 2

Descriptive statistics will be used to present the antenatal, intra partum, post partum, neonatal and follow-up characteristics, including plasma sulfate and magnesium concentration, of the cohort. Bivariate relationships will be explored between these characteristics and CP and adverse motor/cognitive/language/behavioural outcomes. Mixed-effects regression models will examine the association between plasma sulfate and magnesium concentrations at 7 days of age with adverse outcomes; site will be included as a random effect, with characteristics known to be associated with the outcome from literature and clinical experience, as well as demonstrating an association in bivariate analyses, included as fixed effects. The number of factors included will be restricted dependent on the prevalence of the outcome. Both unadjusted and adjusted effect estimates will be presented, along with 95% CIs, and p values for the primary model examining CP. An a priori subgroup analysis for <28 weeks versus ≥28 weeks will be undertaken.

#### Primary aim 3

Receiver operator characteristic (ROC) curves will be constructed, using CP/motor delay/cognitive delay/language delay/behavioural difficulties as individual outcomes, and the sulfate concentration as the predictor. The area under the ROC curve (AUROC) will be calculated and presented, along with the 95% CIs. The sulfate concentration that results in the best combination of sensitivity and specificity will be calculated (Youden’s index) for each outcome.

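### Sulfate samples from day 6 to day 8 are analysed as one day 7 value, and the stated covariate rule would normally leave out age at sampling; a prespecified timing term is a cheap improvement

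*Protocol article*

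**What the plan says.** - **Exposure.** Methods, blood sample collection for all participants: "A blood sample (0.5 mL) is collected on day 7 of age (±1 day) for plasma sulfate and magnesium measurement". Samples taken up to two days apart therefore count as the same measurement.
- **Time course.** Introduction, section on sulfate deficiency after very preterm birth: pilot concentrations "fell rapidly over the first week after birth, before stabilising and increasing thereafter". In infants exposed to antenatal MgSO4, treatment is described as "boosting sulfate to supra-physiological concentrations at birth which then decay to normal or adequate concentrations". No rate of change is given.
- **Covariates.** Statistical methods, primary aims 1 and 2: site is a random effect, and the fixed effects are "characteristics known to be associated with the outcome from literature and clinical experience, as well as demonstrating an association in bivariate analyses". In addition, "The number of factors included will be restricted dependent on the prevalence of the outcome". Age at sampling is not named.
- **Timing elsewhere.** The sample size section for secondary aim 3 lists, among the predictors of low sulfate, "FEI sulfate in the first week after birth, sampling time-point and absence or presence of known loss of function mutations". So timing is treated as relevant to sulfate there.
- **Data recorded.** Antenatal and neonatal data include date and time of birth and, as a possible influence on sulfate, "date/time of any blood transfusions administered within the blood sampling period". The article does not say that the collection time of the day 7 sample is recorded.
- **Threshold.** Primary aim 3 applies ROC curves and Youden's index to the sulfate concentration, with no timing adjustment described.

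**The concern.** The covariate rule selects on association with the outcome. That suits confounders but misses a variable whose only role is to shift the measured exposure. Age at sampling is such a variable: there is no reason to expect it to cause CP, so it should fail both parts of the rule even when it explains part of the variation in measured sulfate.

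Timing variation left in the exposure and unrelated to CP acts as measurement error. It pulls the odds ratio towards 1 and lowers power. In aim 3 it mixes values from different points on the curve into a cut-point that is meant to suggest a target concentration at 7 days. The sample size makes no stated allowance for error in the exposure.

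Births ran from 2013 to 2020, so the window cannot now be narrowed. Only the analysis can still change.

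**Working it through.** **1. Reproduce the planned sample size.** Inputs from the Sample size section: CP rate p = 0.07, OR 0.74 per SD of sulfate, 80% power, type I error 0.05 (taken as two-sided), continuous predictor, 17% loss.

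n = (1.960 + 0.842)² / [p(1−p)(ln OR)²] = 7.849 / (0.0651 × 0.09066) ≈ 1330.

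The article states 1324, which is within 1%. 1324 / 0.83 = 1595.2, against the stated 1595. By the same formula, power at n = 1324 is Φ(√(1324 × 0.0651) × 0.3011 − 1.960) = Φ(0.836) = 79.8%. This is the baseline.

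**2. Add timing noise.** Let s be the slope of sulfate over days 6 to 8, in between-infant SDs per day, and Var(t) the variance of sampling time. Both are assumptions, because the article gives neither.

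- Reliability L = 1 / (1 + s² × Var(t)).
- Var(t) = 1/3 day² if sampling is uniform over ±1 day, or 2/3 day² if days 6, 7 and 8 are equally likely.
- ln OR per observed SD = ln(0.74) × √L.
- N needed to restore the planned power = 1324 / L.

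The square root applies because the plan states its effect per SD of the analysed predictor. Per unit of the true SD the exponent would be L, which makes the attenuation look larger.

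Example, s = 0.25 with days 6/7/8 equal: L = 1 / (1 + 0.0625 × 0.667) = 0.960. ln OR = −0.3011 × 0.980 = −0.295. Power = Φ(9.284 × 0.295 − 1.960) = Φ(0.779) = 78.2%.

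| Slope (SD/day) | L | OR per observed SD | Power | Evaluable N |
|---|---|---|---|---|
| 0 (plateau) | 1 | 0.740 | 79.8% | 1324 |
| 0.1 | 0.997–0.993 | 0.740–0.741 | 79.7–79.6% | 1329–1333 |
| 0.25 | 0.980–0.960 | 0.742–0.745 | 79.0–78.2% | 1352–1380 |
| 0.5 | 0.923–0.857 | 0.749–0.757 | 76.6–73.5% | 1435–1545 |
| 1.0 | 0.750–0.600 | 0.770–0.792 | 67.8–58.1% | 1766–2207 |

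Each range runs from uniform sampling to days 6/7/8 equal. The last row would mean a shift of two SDs between day 6 and day 8, which is hard to square with a curve said to level off at about that time. It is an outer bound, not an estimate.

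**3. Use the pilot SDs as a stand-in.** The secondary aim 1 calculation uses SDs of 154 (exposed) and 32 (unexposed), with the day of measurement not stated. Slopes below are in the same units per day.

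- SD 32: a slope of 5 gives power 79.5–79.2%; a slope of 20 gives 74.8–70.2%.
- SD 154: a slope of 20 gives 79.6–79.4%; a slope of 40 gives 78.9–78.1%.

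The answer turns on a slope that the article does not report.

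**The case against.** **The article makes no mistake here.** A ±1 day window is ordinary. The covariate rule is a general principle that does not forbid a timing term, and a fuller analysis plan may add one. This stands as far as calling it an error goes. But the article does state a rule, and that rule screens on the wrong variable for this purpose.

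**The dilution may be negligible.** The article places stabilisation straight after the first week, so the slope over days 6 to 8 may be small. Day 7 is also a routine blood collection day at the lead site, so samples there may cluster on day 7. Both points stand, and nil belongs in the range.

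**A reader might infer that the effect is materially diluted.** One could assume exponential decay with a half-life of 2 to 7 days, a between-infant CV of 50% and equal sampling on days 6, 7 and 8. Reliability is then 0.74 to 0.97. The documents support none of these inputs. Decay towards zero also conflicts with the article's account of a fall to normal or adequate concentrations. Even then, a planning OR of 0.736 becomes only about 0.77 to 0.74 per observed SD.

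**A reader might also infer bias**, if sampling time or transfusion follows sickness or site routine. Nothing in the article shows this. Transfusion that tracks sickness may well be associated with CP and so pass the covariate rule.

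**Over-adjustment.** Letting the age slope differ by MgSO4 exposure would ordinarily bring exposure itself into the primary model. The article describes exposure as a major driver of neonatal sulfate, so this could remove much of the contrast under study. With about 93 expected CP cases (7% of 1324) and a cap on covariates, it would also use scarce terms. This objection stands, and the fix avoids those slopes.

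**Conclusion.** The point holds as a gap in a stated rule. The window spans the end of a rapid fall in sulfate, and a rule based on association with the outcome would normally drop the variable that accounts for timing within that window. If timing is unrelated to CP risk, the effect is attenuation.

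Its size cannot be derived from the article. Under the assumptions shown, the loss is nil with a plateau by day 6, 0.8 to 1.6 power points at 0.25 SD per day (79.8% to 79.0–78.2%), and 3.2 to 6.3 points at 0.5 SD per day (79.8% to 76.6–73.5%). The article does not support saying that the primary analysis is materially diluted or biased, or that the window itself is wrong.

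This is a cheap improvement: a low-cost precaution against a loss of unknown size.

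**What to change.** - **Aims 1 and 2.** In Statistical methods, state that postnatal age at sampling enters every model using day 7 sulfate or magnesium as a prespecified fixed term, whatever its bivariate association with the outcome. Use hours from birth if collection time is available, otherwise day of age.
- **Aim 3.** As a sensitivity analysis, report the threshold also for sulfate standardised to day 7: observed value − b × (age at sampling − 7 days), with b estimated from the cohort.
- **Do not** force MgSO4-specific age slopes into the primary outcome model. A common slope may leave some timing noise if exposed and unexposed infants differ, but it keeps the sulfate contrast intact.
- **Optional.** A sensitivity analysis excluding samples drawn after a transfusion, using the transfusion times already recorded.

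The cost is analysis wording and about one degree of freedom. It assumes that sample time or day can be retrieved, for example from specimen records. The article records time of birth but does not say that sampling time is recorded, so this should be confirmed first.

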#### Additional biological sample collection for participant subsets to address the secondary aims

Parents at the lead study site (MMH) are approached to provide additional consent for multiple neonatal samples for pharmacokinetic studies (figure 1). A subset of these are offered the option to also consent to collection of maternal and infant blood samples for genetic studies (*SLC13A1* & *SLC13A4* gene variants). To be eligible for this subset, mothers had to have received complete loading and maintenance (at least 24 hours) doses of MgSO_4_ (figure 1).

Blood and urine samples are collected on days 3 (48–72 hours), 7, 14, 28 (figure 1). These days correspond to routine blood collections as per clinical guidelines at the lead study site. Urine samples are collected by placing a cotton wool ball in the nappy. When wet, the cotton ball is placed in a sterile container. Sulfate and creatinine are measured in urine and plasma samples for calculating the FEI sulfate. Magnesium is also measured in all plasma samples.

From October 2018 ‘day 1’ blood and urine samples are collected and stored on admission or within 24 hours of age for all NICU admissions 24–32 weeks gestation. The SuPreme Study information and consent process offers the option to consent to this ‘day 1’ sample being processed (figure 1). If consent is not obtained, the ‘day 1’ samples are discarded.

### Follow-up procedures

When participants are 12–14 weeks CA, parents record two videos of their infant at home via the BabyMoves app^43^ which provides a notification reminder when each video is due and uploads the videos for scoring (figure 1). Videos are scored independently by two expert assessors according to Prechtl’s method of qualitative assessment of general movements, fidgety period.^38^ Each assessor observes both videos of an infant and independently assigns one score; fidgety movements present (FM+)/fidgety movements absent (FM−)/abnormal fidgety movements. In the case of disagreement between the assessors, a third independent assessor reviews the videos. The assessors are not staff members at any of the recruitment centres, and are blinded to any clinical information, other than all infants being VP/EP and their CA when the video was taken. Infants assigned ‘FM−’ are identified as ‘high risk of CP’ and appropriate clinical referrals are made. If there is subsequently no further follow-up information regarding formal diagnosis of CP, these infants are classified as having CP.

Subsequent follow-up is arranged with the child’s main caregiver (biological mother in most cases).

Participants undergo a comprehensive face-to-face neurodevelopmental assessment at 2 years CA (figure 1).

A formal diagnosis of CP (or absence thereof) is established by clinical neurological examination by a paediatrician/neonatologist. If CP is diagnosed, the motor type, distribution and functional level on the Gross Motor Functional Ability Classification System (GMFCS) are recorded.^44 45^

Formal assessment of motor, cognitive and language outcomes is conducted using the Bayley Edition III/4^A&NZ^.^39 40^ Scores are calculated using CA.

Deafness and blindness are ascertained by caregiver report and paediatrician/neonatologist assessment, plus ophthalmology/audiology reports if available.

Social/behavioural outcomes are assessed through caregiver completion of the SDQ.^41 42^

If assessment at 2 years CA has not been attended, caregivers are invited to attend at any point thereafter. If the child is beyond the age range for the Bayley assessment, cognitive assessment is performed using the Wechsler Preschool and Primary Scale of Intelligence (WPPSI-IV^A&NZ^).^46^

Children enrolled in standardised routine neurodevelopmental follow-up (EP or birth weight below 1000 g) may also have a face-to-face assessment at 4 years CA using WPPSI-IV^A&NZ^ plus a neurological examination, and these data are also collected if available.

If face-to-face assessment is declined or not achieved, information is obtained by telephone interview with the child’s caregiver which includes questions on medical and developmental history, any CP diagnosis, and by standardised caregiver-completed developmental questionnaire (Ages and Stages Questionnaires (ASQ-3)^47^) and social/behavioural screening questionnaire (SDQ^41 42^). Telephone interviews are conducted by a psychology graduate who also has training and experience in telephone counselling, to optimise caregiver engagement. The ASQ-3^47^ is presented according to CA. CP is classified as ‘none’ if the caregiver reports that child was walking before 18 months CA and at the time of the telephone interview is running without difficulty and able to kick a ball with either foot. If the caregiver reports a diagnosis of CP, permission is sought to obtain further information from the child’s treating physician regarding CP diagnosis, motor type, distribution and GMFCS level. If the caregiver reports any motor difficulties, or if there are developmental concerns on the ASQ-3, the caregiver is encouraged to attend for face-to-face assessment, and if available these results are then used in place of ASQ-3 scores.

The COVID-19 pandemic resulted in temporary suspension of some follow-up services in 2020. As a result, follow-up data collection will continue until September 2023. This has delayed the age of formal follow-up assessment for some children, and some caregivers opted for telephone interview only, including ASQ-3 and SDQ.

